## A diagram of the study design is shown below.

## A specific statement of primary and secondary endpoints:

The primary endpoint is reduction in excretion at days 3,7 and 14 post- challenge dose of vaccine poliovirus administered 28 days after a single dose of bOPV or IPV.

The secondary endpoints are:

- Increase of sIgA in gingival fluids and stools 28 days after a dose of bOPV or IPV.
- Increase in poliovirus antibody secreting cells (measured with ELISPOT) 7 days following a dose of bOPV or IPV.
- Seroconversion or antibody titer boosting 28 days following a single dose of bOPV or IPV.

A description of what kind of trial:

This is a randomized controlled unblinded trial.

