## Subject withdrawal criteria (terminating investigational product treatment/trial treatment) and procedures specifying 1) when and how to withdraw subjects; 2) the type and timing of the data to be collected for withdrawn subjects; 3) whether and how subjects are to be replaced; 4) the follow-up for subjects withdrawn from investigational product treatment/trial treatment:

As mentioned above, subjects may withdraw from the study at any point. The data collected for withdrawn subjects, in addition to standard questionnaire data, will include the reason for withdrawal. Subjects will not be replaced. No additional follow-up is envisioned for withdrawn subjects. If children miss a scheduled blood sample collection, they will be excluded from final analysis. Children missing a stool or gingival fluid sample but having other samples available will be included in the study. If children develop an acute illness during the study, medical treatment will be provided as explained on page 20, and sample collection will continue as scheduled, unless the illness is associated with a contraindication for venepuncture or the parents refuse sample collection. In this case, the study subject will be withdrawn from the study as explained above.

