# Assessment of Efficacy

## Specification of the efficacy parameters:

Humoral immunity: Sera collected at study entry (day 0) and during the 7-, 28- and 56-day visits, will be examined for the presence (detectable) or absence of neutralizing antibodies to all three poliovirus serotypes. A reciprocal titer of 8 is considered to indicate the presence of neutralizing antibodies. In addition, a change from non-detectable (reciprocal <8) to detectable (reciprocal >8), or from below the highest dilution tested (reciprocal <1448) to the highest dilution tested (reciprocal >1448) will also indicate seroconversion. Although highest titre for neutralizing antibodies is 1024, we are taking end point dilution of half a log higher then 1024. This log of 10.5 is the highest observable titre and is being used because of high titres observed in this highly immunized population.

For participants with detectable antibodies, antibody boosting is defined as a >4-fold increase.

Mucosal immunity: Stool specimens will be collected at 0, 28, 31, 35 and 42 day visits. The samples will be examined for the presence or absence of polioviruses and other enteroviruses. In positive samples, the virus type will be determined following standard protocols from the World Health Organization (WHO) [20]. In addition, the amount (titration) of virus particles will be measured in those samples positive for poliovirus.

Semi-quantitative levels of sIgA in gingival fluid and stool samples will be determined using ELISA. High, medium and low levels will be determined and correlated in each study subject with serum antibody levels and with virus shedding after the challenge (Annex VIII-IX).

Additionally, in a subset of children 10-11 years of age, blood samples collected on days 0 and 7 will be tested to detect the amount of antibody-secreting lymphocytes specific for poliovirus using the ELISPOT technique.

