## Procedures for accounting for missing, unused, and spurious data:

We will do "Modified Intention to Treat Analysis". All evaluable subjects will be included in the analysis. Evaluable subjects will mean the subjects who complete all study requirements including all study visits and provide sufficient quantities of sera samples for analysis. The subjects where sera are available, but missing a stool or gingival fluid sample, will also be included in the analysis.

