## The selection of subjects to be included in the analysis (e.g., all randomized subjects, all doses subjects, all eligible subjects, evaluable subjects):

As stated above, only subjects who complete all study requirements including all study visits and provide sufficient quantities of sera samples for analysis will be included in the analysis.

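### Missed blood samples, not stools, decide who enters the stool-based primary analysis; this discards observed primary outcomes and leaves the comparison open to selection bias

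*Protocol*

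**What the plan says.** The protocol's statement of endpoints makes the primary outcome a stool measure: "The primary endpoint is reduction in excretion at days 3,7 and 14 post- challenge dose of vaccine poliovirus". The efficacy-parameter section fixes the schedule: "Stool specimens will be collected at 0, 28, 31, 35 and 42 day visits". The last primary-endpoint specimen is therefore taken on day 42.

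Under Trial Design, blood is drawn on days 0, 28 and 56. About 175-200 children aged 10-11 years have a further draw on day 7 for the ELISPOT test.

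Three sections then define who is analysed:

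- **Subject withdrawal criteria:** "If children miss a scheduled blood sample collection, they will be excluded from final analysis". The next sentence goes the other way for the other specimens: "Children missing a stool or gingival fluid sample but having other samples available will be included in the study".
- **Procedures for accounting for missing, unused, and spurious data:** the approach is named a modified intention-to-treat analysis, but "Evaluable subjects will mean the subjects who complete all study requirements including all study visits and provide sufficient quantities of sera samples for analysis". The stool exception is then repeated: "The subjects where sera are available, but missing a stool or gingival fluid sample, will also be included in the analysis".
- **The selection of subjects to be included in the analysis:** "only subjects who complete all study requirements including all study visits and provide sufficient quantities of sera samples for analysis will be included". The stool exception does not appear here.

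Annex II specifies a two-tailed chi-square test of excretion after the challenge and defines no separate set for it.

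**The concern.** Eligibility for an analysis should depend on having the outcome being analysed. Here a different specimen decides it, and one of the deciding draws comes after the outcome is complete. The rule deletes primary outcomes that were observed and keeps children whose primary outcome may be missing.

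The exclusion happens after randomisation, and the trial is unblinded, with an injection arm, an oral arm and a no-vaccine arm. The withdrawal section itself names illness that contraindicates venepuncture, and parental refusal, as reasons for losing samples. Families know which arm they are in, so refusal of later draws could differ by arm. If it is also related to excretion, the arms in the analysed set are no longer comparable. Calling the set modified intention-to-treat would lead a reader to expect more protection against this than the definition gives.

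**Working it through.** **1. Timing.** The challenge is on day 28, so stools 3, 7 and 14 days later fall on days 31, 35 and 42. The last scheduled draw is day 56, and 56 − 42 = 14 days.

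| Child | Post-challenge stools | Blood | Under the withdrawal and missing-data sections |
|---|---|---|---|
| A | all three | day 56 missed | excluded |
| B | all three | day 7 missed (ELISPOT subset) | excluded |
| C | one or more missing | complete | included |

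Child C is also excluded if the subject-selection section is read literally. Children A and B have the full primary outcome; child C does not.

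**2. The plan's own sample size.** Annex I gives 89 per cell for control 0.30 against vaccinated 0.10. Use the two-sided formula with alpha 0.05:

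n₀ = [z(0.975)·√(2p̄(1−p̄)) + z(power)·√(p₁(1−p₁)+p₂(1−p₂))]² / (p₁−p₂)²

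with continuity correction n = (n₀/4)·[1 + √(1 + 4/(n₀·|p₁−p₂|))]².

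- At power 0.89 (Annex I, item 6), n₀ = 79.3 and n = 89, as stated. At power 0.90 (item 3) the result is 92.
- The same formula at 0.90 returns the table's other entries, 119 (0.40 against 0.20) and 134 (0.50 against 0.30).
- Drop-out: 89/0.85 = 105 and 89/0.80 = 112. Enrolling 110 tolerates 1 − 89/110 = 19.1% loss.

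**3. Power with and without the losses.** Power of the uncorrected Pearson chi-square test is summed exactly over two binomial distributions, two-sided at 0.05. If the whole 20% drop-out is charged to the blood rule, 110 × 0.80 = 88 remain per cell.

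| Control against vaccinated | n = 110 | n = 88 |
|---|---|---|
| 0.30 against 0.10 (design case) | 0.969 | 0.927 |
| 0.40 against 0.20 | 0.906 | 0.838 |
| 0.50 against 0.30 | 0.860 | 0.789 |

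The step from 110 to 88 is an upper bound on the rule's cost, because a child who leaves before day 31 gives no post-challenge stool under any analysis set. The protocol gives no count of children who would supply stools but miss a draw.

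**4. Bias, under stated assumptions only.** Let p be true excretion in an arm, e the fraction excluded and q excretion among those excluded. Excretion in the analysed set is (p − e·q)/(1 − e). Assume no vaccine effect, with p = 0.30 in both arms and the same e in both.

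- q = 0.30 in both arms: no bias at any e.
- q = 0.50 vaccinated, 0.30 control, e = 0.10: vaccinated (0.30 − 0.05)/0.90 = 0.278, control 0.300, a false reduction of 2.2 points.
- Same q, e = 0.20: vaccinated (0.30 − 0.10)/0.80 = 0.250, a false reduction of 5.0 points.

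The sign can also go the other way. With true excretion 0.30 control and 0.10 vaccinated, e = 0.10, and excluded children excreting at 0.50 and 0.10 respectively, control becomes (0.30 − 0.05)/0.90 = 0.278 and the 20-point effect shrinks to 17.8 points. None of these values of q comes from the documents.

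**The case against.** **The trial keeps its planned power in the case it was designed for.** This stands. Annex I treats 30% against 10% as most likely, and 0.927 at 88 per cell exceeds 0.90. The lower values at 40% against 20% and 50% against 30% arise mainly because 89 was chosen over 119 or 134. They should not be laid at the door of this rule.

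**Most drop-outs are lost anyway.** This also stands. The expected 15-20% drop-out is 148.5-198 of 990 children, and a reader might infer that all of them are lost needlessly. They are not: families who leave provide no later stools, and the day-28 blood is taken before the challenge. The avoidable losses are mainly missed day-56 draws, missed day-7 draws in the subset and insufficient serum, for which no figure is given.

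**Bias is not demonstrated.** Correct. A reader might infer that the primary result will be biased towards the vaccines. That requires missed draws to be related to both arm and excretion, and the documents contain no such evidence. Laboratory investigators are blinded to the samples. The day-7 draw falls three weeks before the challenge and is not tied to one arm, so it may cost numbers without biasing the comparison.

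**The sections need not contradict each other.** The subject-selection section refers back to what was stated earlier, so it can be read as carrying the stool exception with it. The fair description is inconsistent wording, not a proven contradiction.

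**Missing stools can be left to the analysis plan.** Largely accepted. The Statistics section compares excretion at each collection point, so a child without that day's stool simply has no value there, and further detail may sit in a plan not shown. That does not answer the blood rule, which the protocol states outright.

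**Conclusion.** The point holds as a defect in a stated rule. Blood samples govern entry to a stool-based primary analysis, observed primary outcomes are discarded after randomisation in an unblinded trial, and the modified intention-to-treat label does not fit what is essentially a completers definition.

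The comparison is open to selection bias. Its size and direction are unknown from the documents, and it is zero if missed draws are unrelated to excretion. The cost in power at the design case is at most 0.969 to 0.927, assuming 20% loss all attributable to the rule. This should be fixed before results by arm are known, but it does not by itself invalidate the trial.

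**What to change.** Reword the three sections on withdrawal, missing data and subject selection so that they agree and define sets by endpoint:

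- **Primary set:** all randomised children who received the day-28 challenge and have post-challenge stool results, analysed as randomised regardless of any blood sample. These conditions also follow randomisation, but they are intrinsic to a post-challenge stool outcome; a day-56 draw is not.
- **Partly missing stools:** at each collection point, use the children with that day's stool. For any-excretion comparisons, state how a child with some stools missing is classified, do not count missing as negative, and add a sensitivity analysis.
- **Serology:** apply the serum requirement only to the serological endpoints.
- **Completers:** keep this set as a supportive per-protocol analysis and drop the modified intention-to-treat label for it.

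The cost is wording in three sections, with no new children, specimens or visits. The blood requirement would no longer remove any observed primary outcome.

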# Treatment of Subjects

## The treatment to be administered, including the name of all products, the dose, the dosing schedule, the route/mode of administration, and the treatment periods, including follow-up:

See above.

## Medications/treatments permitted (including rescue medication) and not permitted before and/or during the trial:

There will be no restrictions in using medications/treatments. A diagnosis of a B-cell immunodeficiency disorder would lead to exclusion from the study.

## Procedures to monitor subject compliance:

All interventions will be conducted by study personnel; the only subject compliance required is to abide by scheduled visits.

# Assessment of Efficacy

## Specification of the efficacy parameters:

Humoral immunity: Sera collected at study entry (day 0) and during the 7-, 28- and 56-day visits, will be examined for the presence (detectable) or absence of neutralizing antibodies to all three poliovirus serotypes. A reciprocal titer of 8 is considered to indicate the presence of neutralizing antibodies. In addition, a change from non-detectable (reciprocal <8) to detectable (reciprocal >8), or from below the highest dilution tested (reciprocal <1448) to the highest dilution tested (reciprocal >1448) will also indicate seroconversion. Although highest titre for neutralizing antibodies is 1024, we are taking end point dilution of half a log higher then 1024. This log of 10.5 is the highest observable titre and is being used because of high titres observed in this highly immunized population.

For participants with detectable antibodies, antibody boosting is defined as a >4-fold increase.

Mucosal immunity: Stool specimens will be collected at 0, 28, 31, 35 and 42 day visits. The samples will be examined for the presence or absence of polioviruses and other enteroviruses. In positive samples, the virus type will be determined following standard protocols from the World Health Organization (WHO) [20]. In addition, the amount (titration) of virus particles will be measured in those samples positive for poliovirus.

Semi-quantitative levels of sIgA in gingival fluid and stool samples will be determined using ELISA. High, medium and low levels will be determined and correlated in each study subject with serum antibody levels and with virus shedding after the challenge (Annex VIII-IX).

Additionally, in a subset of children 10-11 years of age, blood samples collected on days 0 and 7 will be tested to detect the amount of antibody-secreting lymphocytes specific for poliovirus using the ELISPOT technique.

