**Preparation**

In the week or two preceding the test runs:

1. Assign sera randomly to each run using a balanced block randomization scheme.
2. Use the list generated by the randomization to label plates. This protocol has a diagram of the plate set-up. Each test serum is run in triplicate; so 4 sera may be put on each plate. Each plate is duplicated two more times for the other 2 poliovirus serotypes. There will be a back-titration plate for each serotype, and one cell control plate.

| RUN | P1 Plate | P2 Plate | P3 Plate | Position | DASH # |
| --- | --- | --- | --- | --- | --- |
| 420 | 5 | 22 | 39 | 1 | 99010332 |
| 420 | 5 | 22 | 39 | 2 | 99010327 |
| 420 | 5 | 22 | 39 | 3 | 99010362 |
| **420** | **5** | **22** | **39** | **4** | **99010370** |
| 420 | 6 | 23 | 40 | 1 | 99010376 |
| 420 | 6 | 23 | 40 | 2 | 99010341 |
| 420 | 6 | 23 | 40 | 3 | 99010378 |
| 420 | 6 | 23 | 40 | 4 | 99010371 |
| 420 | 7 | 24 | 41 | 1 | 99010348 |
| **420** | **7** | **24** | **41** | **2** | **387001** |
| 420 | 7 | 24 | 41 | 3 | 99010363 |
| 420 | 7 | 24 | 41 | 4 | 99010383 |

1. In this example of a randomized sample list, serum sample number 99010370 will be in run number 420, position 4 on plates 5 (P1), 22 (P2), and 39 (P3). The IRS is in position 2 on plates 7 (P1), 24 (P2), and 41 (P3).
2. Label caps of 1.7ml microcentrifuge tubes with last 4 digits of the DASH number in the order generated by the randomized list.
3. Prepare MEM 2% FBS (add 20ml fetal bovine serum to 1000 ml bottle of EMEM) Serum must be inactivated at 56°C for 30 minutes and filtered with a Nalgene filter 450-0020.

Tuesday prior to each test run:

Seed T-150 flasks with 30ml of Hep2-C cells at 5x105 cells/ml. Cells must be ordered at least 10 days and up to two months ahead of time through the SRP website: https://srpapps.cdc.gov. The CDC Cell Culture Development Team prepares cell suspensions at a concentration of 5 x 105 cells/ml. Seed enough flasks to have ~1 or 2 flasks for 20 plates.

One day before test run:

1. Aliquot 70 µl test sera into pre-numbered microcentrifuge tubes and inactivate at 56°C for 30 minutes, store at 4°C.
2. Thaw IRS (In House Reference Serum) and dilute 1:8. (IRS has been previously inactivated at 56°C for 30 minutes and is stored at -70°C)
   - 280µl aliquots - add 1960 µl MEM 2% FBS day of test
   - 375µl aliquots - add 2625 µl MEM 2% FBS day of test

Day of test run:

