1. Add 490µl MEM 2% FBS to 70µl heat inactivated test sera aliquots (for a final dilution of 1:8).
2. Add 25µl MEM 2% FBS to rows B-H of the test plates with multichannel pipette.
3. Add 25µl MEM 2% FBS to each row of back titration plates (S1, S2 and S3).
4. Add 50µl MEM 2% FBS to every well of the cell control plate.
5. Add 50µl MEM 2% FBS of each serum dilution (1:8) to row “A” only of the test serum plate (3 well/serum dilution and 4 test sera per plate – see figure).
6. Repeat this procedure for the poliovirus type 2 and type 3 test serum plates.
7. Make serial 2-fold dilutions with Cetus dilutor from row A through row H (serum dilutions will range from 1:8 to 1:1024).
8. Dilute each poliovirus serotype in MEM 2% to contain 100 TCID50 according to figure below. Prepare sufficient virus challenge suspension for the number of sera to be tested; each plate requires approximately 2.5ml of diluted challenge virus.
9. Prepare the back titrations of each poliovirus serotype in MEM 2% FBS. Titrate each virus from 100 TCID50 a further three 10-fold steps. (see figure below)
10. 10.

| **Virus Stock** In Hep2-C | Aliquoted 08/09/99 | | | 1000µl/vial | |  |  |
| --- | --- | --- | --- | --- | --- | --- | --- |
| **Sabin 1** 100 TCID50 = 10-5.2 |  |  | | 100 | 10 | 1 | 0.1 |
| virus 633µl 100µl | 100µl | 100µl | 800µl  5.4ml 45ml | 7ml | 100µl | 100µl | 100µl |
| medium 367µl 900µl | 900µl | 900µl | 7.2ml | 63ml | 900µl | 900µl | 900µl |
| **Sabin 2** 100 TCID50 = 10-5.35 |  |  |  |  |  |  |  |
| virus 448µl 100µl | 1004µl | 100µl | 800µl  5.4ml 45ml | 7ml | 100µl | 100µl | 100µl  f |
| medium 552µl 900µl | 900µl | 900µl | 7.2ml | 63ml | 900µl | 900µl | 900µl |
| **Sabin 3** 100 TCID50 =10-5.0 |  |  |  |  |  |  |  |
| virus 100µl | 100µl | 100µl | 800µl  5.4ml 45ml | 7ml | 100µl | 100µl | 100µl  _ |
| medium 900µl | 900µl | 900µl | 7.2ml | 63ml | 900µl | 900µl | 900µl |

1. Add 25µl of 100 TCID50 of relevant poliovirus antigen to all wells in the test serum plates.
2. To the back titration plates:

- Add 25µl of 100 TCID50 of virus to rows A and B (*i.e*., 24 wells/dilution)
- Similarly, add 25µl of the next three 10-fold dilutions to rows C and D, E and F, and G and H, respectively.

1. Wrap all plates in plastic wrap and tap gently to mix. Incubate for 3 hours at 36°C and 5% CO2.

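### The humoral rule counts any rise to the assay ceiling as seroconversion, so a seropositive child going from 1024 to 1448 (1.41-fold) is a responder while other seropositive children need a >4-fold rise

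*Protocol*

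**What the plan says.** Protocol, Specification of the efficacy parameters (humoral immunity), gives two routes to seroconversion. The first is "a change from non-detectable (reciprocal <8) to detectable (reciprocal >8"). The second is a change "from below the highest dilution tested (reciprocal <1448) to the highest dilution tested (reciprocal >1448) will also indicate seroconversion". The second route carries no condition on baseline serostatus and no minimum rise.

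The ceiling is explained in the same paragraph: "we are taking end point dilution of half a log higher then 1024", and "This log of 10.5 is the highest observable titre and is being used because of high titres observed in this highly immunized population".

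A separate rule follows for seropositive children: "For participants with detectable antibodies, antibody boosting is defined as a >4-fold increase".

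Protocol, A specific statement of primary and secondary endpoints, joins the two classes in one secondary endpoint: "Seroconversion or antibody titer boosting 28 days following a single dose of bOPV or IPV". A child who meets either rule is a responder. No section reconciles the two rules.

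**The concern.** A child with a reciprocal titre of several hundred is already seropositive, so calling a later ceiling reading seroconversion uses the word in two incompatible senses. The practical difficulty is the missing fold-rise condition. Two seropositive children in the same arm face different standards: one needs more than a 4-fold rise, and the other needs only to cross from just under the ceiling to the ceiling, a step small enough to arise from assay variation.

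The protocol chose this ceiling because it expects high titres. Its Trial Objectives expect the highest humoral immunity at 5-6 years and high titres at 10-11 years, so the band just under the ceiling may be well populated in those groups. The response proportion would then depend partly on how many children start in that band, and unvaccinated controls could be counted as responders on reading variation alone.

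**Working it through.** **Inputs from the protocol.** Ceiling 1448, stated as a log of 10.5 and half a log above 1024; boosting rule >4-fold (Specification of the efficacy parameters). Dilutions and replicates (Annex VII, Preparation): "serum dilutions will range from 1:8 to 1:1024" and "Each test serum is run in triplicate; so 4 sera may be put on each plate".

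**Reproducing the ceiling.** 2^10.5 = 1448.15, which equals 1024 × 2^0.5. Half a log10 above 1024 would be 1024 × 10^0.5 = 3238, so the log is base 2 and the protocol's 1448 is reproduced.

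**Rise needed to reach the ceiling** = 1448.15 / baseline titre:

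| Day-0 titre | log2 | Fold rise to 1448 | Responder by the ceiling route | Responder by the >4-fold rule |
|---|---|---|---|---|
| 1024 | 10.0 | 1.41 | yes | no |
| 724 | 9.5 | 2.00 | yes | no |
| 512 | 9.0 | 2.83 | yes | no |
| 362 | 8.5 | 4.00 | yes | no (exactly 4-fold) |
| 256 | 8.0 | 5.66 | yes | yes |

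The two rules part company at 1448 / 4 = 362. Below 362, a child who reaches the ceiling has risen more than 4-fold and qualifies anyway. From 362 to just under 1448, the ceiling route alone makes the child a responder, always on a measured rise of 4-fold or less. By contrast, 64 to 256 (exactly 4-fold) and 362 to 1024 (1024 / 362 = 2.83-fold) are non-responses.

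**Size of the noise effect (illustration).** The protocol gives no assay SD and no endpoint formula. Assumptions: a true log2 titre that does not change; two independent readings with SD 0.25, 0.5 or 0.75 log2; readings rounded to steps of 1/3 log2 (three wells per 2-fold dilution) and capped at 10.5; 400,000 simulated pairs per scenario. Probability of a false call per serotype:

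| True log2 titre | Ceiling route, SD 0.25 / 0.5 / 0.75 | >4-fold rule, SD 0.25 / 0.5 / 0.75 |
|---|---|---|
| 10.0 | 0.08 / 0.19 / 0.22 | 0.000 / 0.000 / 0.005 |
| 10.17 | 0.19 / 0.23 / 0.24 | 0.000 / 0.000 / 0.003 |
| 10.5 | 0.19 / 0.23 / 0.24 | 0.000 / 0.000 / 0.001 |

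The ceiling route cannot exceed 0.25 in this model: if p is the chance that a reading is at the ceiling, the false-call probability is p(1 − p). Further from the ceiling the effect fades. At a true log2 titre of 9.0 the ceiling route gives 0.000 / 0.004 / 0.036 and the >4-fold rule 0.000 / 0.001 / 0.019.

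**Whole arm.** This rate needs the between-child spread of titres, which the protocol does not give. With an assumed mean log2 titre of 8 to 9.5, between-child SD of 0.75 to 3 and assay SD of 0.25 to 0.5, the ceiling route gives about 0.1% to 8% per serotype and the >4-fold rule about 0.1% or less. At assay SD 0.75, mean 8 and between-child SD 0.75, the order reverses: 1.2% by the ceiling route against 2.0% by the >4-fold rule.

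**The case against.** The rule has an evident purpose. With a 1448 ceiling, no child starting at 362 or above can show a >4-fold rise however strong the response, and a ceiling reading is censored, so the true rise may be larger than the measured one. Simply applying >4-fold to everyone would turn these children into automatic non-responders, again according to baseline titre. This stands, and it shapes the fix. But censoring makes such children unclassifiable on fold rise; it does not show that they responded.

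The protocol also tests each participant's sera on the same plate and in triplicate (Methods and timing for assessing the efficacy parameters), which should reduce within-child variation. That argues for the lower end of the assumed SD range. It does not supply a fold-rise criterion.

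Read literally, a titre above 1448 is impossible if 1448 is the highest observable, so the route could never apply. The surrounding words about reaching the highest dilution make clear that reaching the ceiling is meant.

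A reader might infer more than the documents support:

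- **That a single well decides the result, a 1.26-fold step (1149 to 1448).** This needs an endpoint formula that the protocol does not give. The 1.41 from 1024 to 1448 needs only the protocol's own figures.
- **That a definite share of the control arm will falsely seroconvert.** No such figure can be fixed without the spread of titres, and the range above is wide.
- **That the comparison of arms is biased, or that the endpoint reflects baseline titre rather than vaccine.** Arms are randomized and the laboratory is blinded to samples, so false calls can arise in every arm; no bias in the arm difference has been shown.
- **That all humoral results are affected.** The tests named in the Statistics section and Annex II use seropositivity and titre distributions, not this rule.

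**Conclusion.** The definition is internally inconsistent and, followed as written, misclassifies some seropositive children: a 1.41-fold rise to the ceiling is a response, while a 4-fold rise below it is not. That rests on the protocol's own figures. The inconsistency is confined to day-0 titres from 362 to just under 1448. The false-call probability of about 0.08 to 0.25 per serotype, against at most about 0.005, applies to a child with a stable true titre of 2^10 to 2^10.5 and rests on the assumed SD and reading steps; it is not a rate for a whole arm. The consequence is limited to the seroconversion-or-boosting secondary endpoint. The primary excretion endpoint and the sample size do not depend on it. It should be corrected before the serology is analysed.

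**What to change.** In Specification of the efficacy parameters:

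1. Keep seroconversion for the change from undetectable to detectable, and delete the ceiling route from that definition.
2. Apply one fold-rise criterion to every child who is seropositive on day 0.
3. Restrict the boosting denominator to seropositive children whose day-0 titre leaves room to observe a >4-fold rise, that is, below 1448 / 4 = 362.
4. Report children starting at 362 or above separately by arm and age group, with the number who reach the ceiling and the number already there on day 0.

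Steps 3 and 4 belong with step 2; without them, high-titre children become non-responders by construction. The cost is a change of wording, with no new samples or assays. The boosting denominator will be smaller, perhaps markedly so in the age groups expected to have high titres, and the stated response rate somewhat lower.
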